#### Trait and state components of approach bias

The third set of research questions relates to the state and trait components of approach bias and is examined within the control group only. This is because only participants in the control group receive measurement AATs throughout the study period. Multilevel models test whether bias size and negative emotions are related on both a between-subjects and a within-subjects level and to what degree this depends on the strength of the desire for these foods. A separate model tests equivalent research questions for the relation between bias strength and craving, as well as bias strength and intake, respectively. The latter analyses testing how bias strength is related to subsequent food intake are expanded by including trait and day-level impulsivity and day-level intentions of regulating food intake.

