**Methods and analysis:**

Participants who aim to change their eating behaviour are randomised to intervention or control groups. They complete six sessions of a smartphone-based AAI, in which they push (ie, avoid) or pull (ie, approach) personalised food images. Intervention group participants always avoid foods that they personally want to eat less often and approach foods that they personally want to eat more often. In the control group, images are paired equally often with both response directions. To evaluate contextual and dynamic intervention effects, ecological momentary assessment (EMA) is measured throughout, with questions about food intake, hunger, stress, emotions, eating intentions, food craving and impulsivity twice a day. Additional EMA preintervention and postintervention measures are administered before and after the intervention phase (4 days each) with a 1-day follow-up EMA 4 weeks after the intervention. Multilevel models will examine the temporal covariance between approach bias and self-reported variables as well as short-term and long-term intervention effects on approach bias, food intake and craving.

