One recent AAT variant does not require swiping movements on the touchscreen, but instead requires participants to physically move the phone towards or away from themselves while viewing food stimuli.^27 59–61^ This task has been shown to be a valid tool to measure food approach biases outside the laboratory and to provide relevant information beyond self-report measures.^59^ In addition to RTs, it also yields data on the force of the movements, which might contain relevant information not captured by RTs.^61^

The study presented here sets out to test its effectiveness as an intervention tool for AAI; that is, when it is programmed to pair the foods that a specific participant wants to eat more often with approach, and to pair the foods that a specific participant wants to eat less often with avoidance responses. Specifically, we will study to what degree the intervention can support participants in their goal of changing their eating behaviour. We further examine the reliability and validity of approach bias scores obtained through a phone-delivered AAT. Combining the AAI/AAT with the repeated measurement of related phenomena through EMA allows us to disentangle short-term and long-term intervention effects as well as to investigate whether approach bias covaries with intake-related variables over time.

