**Figure 2 F2:**
[figure not shown]
Illustration of the task. On approach trials, participants move the phone closer to themselves (central image), on avoidance trials, they move it away from themselves (image on the right; adapted from Zech *et al* [61]).

The active and sham AAT trainings feature 4 out of 6 approach-foods, 4 out of 6 avoid-foods, as well as 8 out of 12 control object stimuli. The training sessions consist of four training blocks of 16 trials each, and each training block is preceded by 4 practice trials, yielding a training session of 64 training trials and 16 practice trials, or 80 trials total. The pre-, post- and follow-up bias assessment AATs similarly consist of four blocks preceded each by four practice trials but feature all selected images (6 ‘increase-foods‘, 6 ‘decrease-foods’ and 12 objects). All 24 images are presented one time per block, yielding 96 test trials and 16 practice trials, or 112 trials total. In all AATs, the instructions of the blocks alternate such that participants are instructed to approach foods while avoiding objects in the first block (approach-food blocks) and avoid foods while approaching objects in the second block (avoid-food blocks). This order is the same for all sessions and all participants. Crucially, in the active training AATs, only approach-foods are shown in the approach-food blocks, while only avoid-foods are shown in the avoid-food blocks; sham training instead features both approach-foods and avoid-foods during both approach-food and avoid-food blocks. Completing one session of the AAT/AAI takes about 5 min.

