Have you spent more money today than you wanted to?	X	X	X	X
Have you felt impatient today?	X	X	X	X
Have you made a spontaneous decision today?	X	X	X	X
How strong has your craving for this food been *since the midday questionnaire*?*			X	
How much of this food have you eaten *since the midday questionnaire*?*			X	
How much do you expect that this task will help you reach your dietary goals?†	X†			
Throughout the whole study, how often did you push this food away from yourself?*				X
Please indicate the day your last period started.				X

All items are answered on a slider from 0 to 100 unless indicated differently in parentheses. Midday prompts remain the same across the entire study duration. Evening prompts differ depending on the study phase as indicated:.

*These items are asked alongside a food image and are repeated for each image (six ‘increase-food‘ and six ‘decrease-food’ images).

†This item is only asked after the first and the last AAT session (days 5 and 15).

AAT, Approach Avoidance Task; EMA, ecological momentary assessment.

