### Outcomes

#### Main outcomes

This study uses three main outcome measures. The first outcome measure is participants’ self-reported intake of ‘increase’ and ‘decrease’ foods according to the EMA schedule outlined above, on a slider from 0 (labelled ‘nothing’) to 100 (‘very much’). The second outcome measure is participants’ self-reported craving for those same foods in the same manner. Simple, single-item measures reduce participant burden but might negatively affect reliability. To ameliorate this, measures are applied for each food separately. Time trends that might indicate changes in participants’ perceptions of amounts as ‘much’ or ‘little’ will be checked in the control group and, if present, controlled for in analyses.

The third outcome measure is the approach bias for all selected foods based on the RT and force in the AAT. The RT is defined as the time from picture onset to movement onset. Force is defined as the peak acceleration in the correct direction during a trial, standardised within participant by dividing every individual’s measurement of force by the participant-specific SD. Separately for approach and avoidance trials as well as for sessions, the RT and the force will be averaged across the four AAT blocks for each specific food stimulus. For objects, we will also average across the different stimuli. The average approach or avoid response for objects on a session will be subtracted from stimulus-specific food approach or avoidance response on that session to achieve food-specific *single-difference* approach and avoidance scores according to these formulas:

Stimulus−specificavoidance=[food−specificavoidance]−[averageobjectavoidance]

Stimulus−specificapproach=[food−specificapproach]−[averageobjectapproach]

*Double-difference scores* will be used as a full bias score per food stimulus and session, according to the formula: ((food-specific avoidance)−(food-specific approach))−((average object avoidance)−(average object approach)).

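### As described, the control-group bias-craving and bias-intake models do not separate stable differences between a person's foods from change over time

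*Protocol article*

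**What the plan says.** Under *Trait and state components of approach bias*, the control-group models first ask whether bias and negative emotions are "related on both a between-subjects and a within-subjects level". The section then extends this: "A separate model tests equivalent research questions for the relation between bias strength and craving, as well as bias strength and intake, respectively". No further level is named for these models.

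The measurements are finer than that split:

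- **Bias.** *Main outcomes* says that double-difference scores "will be used as a full bias score per food stimulus and session". Averaging across stimuli is planned for objects; food scores stay food-specific.
- **Craving and intake.** The footnote to Table 1 says: "These items are asked alongside a food image and are repeated for each image". There are 12 images per person.
- **Foods per sham session.** *Approach-Avoidance Task* states: "The active and sham AAT trainings feature 4 out of 6 approach-foods, 4 out of 6 avoid-foods, as well as 8 out of 12 control" pictures. That is 8 foods.
- **Sessions.** The abstract states: "They complete six sessions of a smartphone-based AAI".

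The stated aim is temporal. The introduction closes with the intention "to investigate whether approach bias covaries with intake-related variables over time", and the abstract also speaks of covariance over time.

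**The concern.** A deviation from a person's mean bias has two components. One is how a given food usually differs from that person's other foods, which is stable. The other is how that food differs on this day from its own usual level, which is the state component. Someone who always craves chocolate more than carrots, and always pulls chocolate faster, yields a positive within-person slope even if nothing changes from day to day.

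At stake is the third set of research questions: whether bias behaves as a state that moves with craving and intake. If the two components are pooled, a stable food preference can be reported as temporal covariation. The planned extensions with impulsivity and daily intentions build on the same bias-intake slope.

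**Working it through.** The documents state no figure for this analysis, so there is none to reproduce. The check takes the algebra first and then simulation.

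**Inputs from the article.** 150 participants, so about 75 controls if simple randomisation splits evenly (assumption); 8 foods per sham session; 6 sessions.

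**Inputs assumed, because the documents give none.** Total variance 1 for each variable; person share 0.20; stable food share 0.05 to 0.30 for bias (Vb) and 0.30 to 0.40 for craving (Vc); correlation r of 0 to 0.5 between stable bias and stable craving across a person's foods. The true over-time relation is set to zero.

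**Decomposition.** For participant i, food f, session t:

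(session value − participant mean) = (participant-by-food mean − participant mean) + (session value − participant-by-food mean)

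The person-centred slope is a weighted average of the slopes on the two right-hand terms. With no over-time relation and 8 foods × 6 sessions, its expected value is about

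r × √(Vb × Vc) × 7/8 ÷ [Vb × 7/8 + (0.80 − Vb) × 47/48].

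Example with Vb = 0.20, Vc = 0.40, r = 0.3: numerator 0.3 × √0.08 × 0.875 = 0.0742; denominator 0.175 + 0.5875 = 0.7625; slope 0.097. The simulated mean was 0.097.

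**Simulated rejection rates** for the person-centred slope (400 runs per setting, two-sided 5%, participant-clustered standard errors):

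| Stable food share, bias / craving | r = 0 | r = 0.2 | r = 0.3 | r = 0.5 |
|---|---|---|---|---|
| 0.05 / 0.30 | 7.0% | 34.7% | 67.7% | 96.3% |
| 0.10 / 0.30 | 5.2% | 58.5% | 89.0% | 100% |
| 0.20 / 0.40 | 6.2% | 86.0% | 99.0% | 100% |
| 0.30 / 0.40 | 4.8% | 92.5% | 100% | 100% |

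With model-based standard errors, the r = 0 column was about 7% to 15%. Centring at the participant-by-food mean gave a mean slope between −0.001 and 0.001 and 2% to 7% rejection in every setting. The Monte Carlo standard error at 5% is √(0.05 × 0.95 ÷ 400) = 1.1 percentage points.

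**Mixed-model check** (shares 0.20 / 0.40, r = 0.3; only 40 runs):

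- Participant random intercept, person-mean centring: slope 0.10, 100% rejection.
- Participant-by-food random intercept, still person-mean centred: slope 0.025, 30% rejection.
- Three-part split: over-time slope 0.002, 2.5% rejection; stable food slope 0.29, reported separately.

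These results agree with the algebra. The food component's weight is 7/8 × (0.20 + 0.60/6) ÷ 0.7625 = 0.2625 ÷ 0.7625 = 0.344, and 0.344 × 0.29 + 0.656 × 0.002 = 0.101.

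**Check on a millisecond scale.** A sham block of 16 trials shows 8 foods and 8 objects, so each food gets 2 approach and 2 avoidance trials per session. The score error variance is σ²(1/2 + 1/2), plus a shared object term σ²(1/16 + 1/16). Assumed: σ = 150 ms; stable food-level bias SD 20 to 60 ms; stable-food share of within-person craving variance 30% to 70%; r = 0.2 to 0.5. The person-centred slope was significant in 12% to 100% of runs (76% at 40 ms, 50%, r = 0.3). A participant-by-food random intercept without re-centring gave 6% to 47% (r 0.3 to 0.5, share 30% to 50%). Participant-by-food centring gave 4% to 7%.

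**Stimulus effects.** Further runs over r = 0.2 to 0.5 again gave 12% to 100%, against 2% to 10% with participant-by-food centring. Adjusting for stimulus removed the artefact only when preferences were fully shared across people.

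**The case against.** The strongest reply is that the article does not contain the faulted model. *Data analysis plan* describes itself as brief and leaves the exact formulas to a preregistration. A within-subjects level could mean deviation from the person-by-food mean, or bias averaged over foods per session; either would avoid the mixing. This stands. A reader might infer that the models are specified with person-mean centring and nothing else, but the documents do not say so. Averaging over foods does, however, fit poorly with *Main outcomes*, which keeps food scores separate.

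A reader might also infer that the analysis cannot answer its question, or that its error rate is certainly above 5%. Neither is supported. The artefact needs stable food differences in both variables and a correlation between them. The introduction cites a study in which desire for specific foods explained variance in bias, so a non-zero correlation is plausible, but no size is given. *Stimuli* selects foods on recent and intended intake, which makes stable intake differences likely; it does not build in differences in bias or craving.

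Three limits on scope also stand. The bias-emotion model is not affected in this way, because emotions are rated once per prompt and not per food. The intervention-effectiveness comparisons are a separate set of questions. The simulations use the six sham sessions only, and the article does not say whether the 12-food assessment sessions enter as well.

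What does not stand is that this is only an omitted detail: the article names a two-level split for variables that it measures on three.

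**Conclusion.** The point holds for the bias-craving and bias-intake models as the article describes them, and should be settled before analysis. Under person-mean centring, the within-subjects slope combines stable food preference with change over time and does not isolate the temporal covariance that the study aims at. With no temporal relation, the false-positive rate is roughly 12% to 100% for assumed food-level correlations of 0.2 to 0.5, and near 5% at zero correlation when preferences are personal (5% to 7% with clustered standard errors). These figures depend on assumed variance shares and correlations and are not properties of this trial. A stimulus random intercept would remove only preferences that people share, and a participant-by-food random intercept without re-centring reduces the problem but does not remove it. Whether the preregistered formulas already avoid this cannot be judged from the article.

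**What to change.** In the bias-craving and bias-intake models, enter the bias predictor as three terms:

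1. the participant mean;
2. the participant-by-food mean minus the participant mean;
3. the session value minus the participant-by-food mean.

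Include a participant-by-food random intercept. Base every state or temporal claim on term 3 only, and report term 2 as stable food preference. If the preregistration already does this, one sentence in the article saying so is enough.

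The cost is one changed centring step and one extra coefficient. The state slope then uses only variation within a food, so its confidence interval is wider. No change to design or data collection is needed.

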### Patient and public involvement

Patients and the public are not involved in study design, data collection, data analysis, or dissemination.

### Ethics, dissemination and data handling

The study has received ethical approval from the ethics board of the University of Salzburg and is conducted in accordance with the declaration of Helsinki. Results of the trial will be disseminated through a series of articles in appropriate scientific journals and conference presentations.

Data are handled confidentially and stored in a pseudonymised manner. Neither m-path nor the AAT application collect personal data but work through three-digit identification codes assigned to participants. The identification key linking personal data to the identification codes will be kept in password-protected files separately from the pseudonymised data and will be destroyed 1 year after termination of the study. Deidentified data will be archived for at least 10 years and consent forms as documentation of participation will be archived for 30 years. The deidentified data will be made public on the Open Science Framework after the completion of planned publications.
